### Study procedures

#### Intervention group

##### Medication review

The medication of patients in the intervention group will be reviewed by the community pharmacist using the full record of prescription only drugs which were dispensed by the patients' pharmacy and the patients medication evaluation profile. This profile shows when the patients has obtained his medication from the pharmacy. The GP will be consulted by telephone for details about indications for drugs and results from laboratory tests. When prescribed by a medical specialist, details about the indication for the drug will be obtained from the specialist, who will be consulted by the community pharmacist. The National guidelines for treatment of diseases will be used by community pharmacists as a method for performing medication review.

The Pharmaceutical care network Europe DRP-score form will be used to record drug problems. Each drug will be evaluated on adverse reactions, drug choice problems, dosing problems, drug use problems, drug-interactions or other problems. Causes for drug related problems will be assessed and interventions will be made. During the medication review the patient will be involved as a full partner. Any changes made will be communicated with the patient. This method for medication review will be pilot tested before use.

The occurrence of drug related problems will be discussed with the GP. The result may be an adaptation of the drug regimen. The medication review will take 10-30 minutes per patient and will depend on the complexity of the medication regimen and problems detected.

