#### Secondary outcome measures

##### Incidence of Re-hospitalization

The total incidence of hospital re-admissions possibly related to medicine during the study period is measured. The incidence of hospital admissions will be derived from general practitioners medical record and determined by self report. The relation to drugs will be derived using a list of selection criteria. Hospital admissions will be classified as related to drugs if:

▪ It is explicitly clarified in the medical notes that the admission is drug related. The specialist of the patient will be consulted to clarify the relation to drugs.

▪ The patients' physician, when asked, indicates that the admission was drug related.

▪ To classify the causality of the hospital admission to the drug, the Naranjo algorithm will be used. The Naranjo algorithm or Naranjo Scale is a questionnaire designed by Naranjo *et al *for determining the likelihood of whether an ADR is actually due to the drug rather than the result of other factors [25]. The causality will be determined by the project leader.

All participating patients are asked to complete 3 validated questionnaires during the research year. The first questionnaire will be sent to the patients one week before the first counselling visit of the pharmacist. The second questionnaire will be sent at 6 months, the third questionnaire will be sent at 12 months. It will take approximately 30 minutes to complete one questionnaire.

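### Classification of readmissions as drug related is not protected from arm knowledge, and the rule combining an ADR scale with two broader criteria is undefined

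*Protocol article*

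**What the plan says.** The protocol article, under Incidence of Re-hospitalization, defines the outcome: "The total incidence of hospital re-admissions possibly related to medicine during the study period is measured". Admissions are found through GP records and self-report. Three items then bear on whether an admission is drug related:

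1. The notes: "It is explicitly clarified in the medical notes that the admission is drug related", with the specialist consulted for clarification.
2. The physician's opinion: "The patients' physician, when asked, indicates that the admission was drug related".
3. The Naranjo algorithm, which the article describes as a questionnaire "for determining the likelihood of whether an ADR is actually due to the drug rather than the result of other factors".

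The list closes with "The causality will be determined by the project leader". The section does not say whether the items are alternatives or must all be met. It also does not say what happens when they disagree.

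Three other places matter. Primary outcome measures assigns DRP assessment to an independent team of clinical pharmacologists. Setting says that the medication review is done with the GP, and the Medication review section adds: "The occurrence of drug related problems will be discussed with the GP". The section on Pharmacotherapeutic Audit Meetings (PTAM) describes three sessions about the intervention, in groups that include 6 to 10 GPs.

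**The concern.** Whether a drug caused an admission is a judgement, and many admissions of older patients on five or more drugs could be argued either way. If those who supply the judgement know more about one arm than the other, the drug-related count can differ between arms without any effect on patients.

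The direction cannot be predicted. A GP who has just helped to tidy a regimen may be less inclined to blame the drugs. A GP who has been shown a list of drug problems may be more inclined to see one.

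The second issue is fit. The trial aims to improve adherence, and its Discussion expects better adherence to lower the risk of rehospitalisation. If an ADR scale decides the classification, an admission caused by not taking a drug has no natural place in the outcome.

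Drug-related readmission is a stated secondary objective, so both issues bear on a result that the trial intends to report.

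**Working it through.** The article gives no rate, effect size or power for readmission, so there is no figure to reproduce. The check sets the text side by side and then illustrates the possible size with assumed rates.

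**Who judges, and what they can know**

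| Contributor | Role in classification | What the article shows about knowledge of arm |
|---|---|---|
| GP of an intervention patient | May be the physician whose opinion counts (item 2); GP record is a source of admissions | Consulted for the review and discusses the problems found, so cannot be masked |
| Physician of a control patient | Same | Not stated |
| Hospital specialist | Consulted on item 1 | Contacted in the intervention arm about drugs that the specialist prescribed; otherwise not stated |
| Project leader | Determines causality | Not stated; neither masking nor independence is mentioned |
| Clinical pharmacologists | None for this outcome (they assess DRPs) | Described as independent |

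Knowledge of arm is certain only in the first row. That is enough for classification to differ by arm, because this physician's opinion is one of the listed items.

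**What the criteria can capture**

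Items 1 and 2 use the broad term of drug relatedness, so an admission due to missed treatment can qualify under either. Item 3 is, in the article's own description, about ADRs. Background lists non-compliance among the causes of DRPs. The outcome therefore has two possible readings:

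- Items as alternatives: adherence-related admissions can be counted.
- ADR scale as a required or final step: they would tend to drop out.

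The text does not choose between them.

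**Illustration 1: recognition differs by arm, no true effect**

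Inputs: 342 patients (from Sample size) at a 1:1 ratio, so n = 171 per arm. Clustering is ignored. Assumed: the same true risk p of a drug-related admission in both arms, and a recognised share of 0.70 in control and s in intervention.

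- Observed risks: a = 0.70p and b = s·p. Observed ratio: b/a = s/0.70.
- s = 0.60: 0.60/0.70 = 0.86. s = 0.50: 0.50/0.70 = 0.71.
- s = 0.80: 0.80/0.70 = 1.14. s = 0.90: 0.90/0.70 = 1.29.

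Rejection rate of a two-sided 5% test: d = |a − b|, SE = √[a(1−a)/n + b(1−b)/n], rate = 1 − Φ(1.96 − d/SE) + Φ(−1.96 − d/SE).

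Example with p = 0.10 and s = 0.50: a = 0.07, b = 0.05, SE = √[(0.0651 + 0.0475)/171] = 0.0257, d/SE = 0.78, rate = 12.2%.

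| True risk p | s = 0.60 | s = 0.50 | s = 0.80 | s = 0.90 |
|---|---|---|---|---|
| 5% | 5.8% | 8.4% | 5.7% | 7.6% |
| 10% | 6.6% | 12.2% | 6.4% | 10.5% |
| 20% | 8.5% | 20.7% | 8.1% | 17.3% |

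**Illustration 2: the ADR scale is decisive**

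Assumed: a share q of true drug-related admissions is due to non-adherence, the intervention halves those, and ADR admissions are unchanged.

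- True ratio = (1 − q) + 0.5q.
- q = 0.10: 0.90 + 0.05 = 0.95. q = 0.50: 0.50 + 0.25 = 0.75.
- Ratio observed if only ADR admissions count: 1.00 in every case.

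**The case against.** The strongest reply is that this is a condensed article. Masking of the assessor for a secondary outcome may stand in the full protocol, and silence here is not evidence of an unmasked rater. That is right about the project leader. A reader might infer that this person knows the allocation, but nothing in the article says so. What stands is narrower: the article fixes who decides, describes no protection, and does describe independence for the DRP outcome. The use of the physician's opinion is also stated positively, not inferred from silence.

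A reader might also infer that adherence-related admissions are necessarily missed. The article does not support this, since two of the three items are broad enough to include them. The loss follows only if the ADR scale is decisive.

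A third tempting reading is that self-reported admissions are found more often in the intervention arm, because its patients have more counselling contacts. The article does not tie the collection of admissions to those contacts. The questionnaires go to all participants, and the cost calendars, which include hospitalisations, are not described as differing by arm.

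Finally, it can be said that all-cause readmission is less specific than the stated objective. This stands as a reason not to make it the lead measure. It is no reason against reporting it alongside.

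**Conclusion.** The concern holds in a limited form. As written, the classification draws on physicians who, in the intervention arm, take part in the intervention. Causality is then settled by a person not stated to be masked or independent. Arm-dependent classification is therefore possible, and its direction is unknown. Separately, the rule for combining an ADR scale with two broader criteria is undefined, so adherence-related admissions may be missed.

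The size cannot be derived from the document. Under the assumed recognition shares, the observed ratio with no true effect runs from 0.71 to 1.29, and the 5% test rejects in 5.7% to 20.7% of trials. If the ADR scale were decisive, a true ratio between 0.95 and 0.75 could appear as 1.00. These figures rest on invented rates and on ignoring clustering. They show what is possible and do not estimate the bias.

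This is a secondary outcome. The point should be repaired, but it does not touch the primary comparison.

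**What to change.** - Have each admission classified from GP and hospital records from which arm, pharmacy and medication-review notes have been removed. The project leader can do this if masked in that way, or the independent pharmacologists already engaged for the DRP outcome can.
- Do not let the opinion of an unmasked physician suffice alone to call an admission drug related.
- State how the three items combine. Apply the ADR scale only to suspected ADR admissions, and add a written criterion for admissions due to non-adherence or under-treatment.
- Report all-cause readmission by arm beside the drug-related subset. Admissions are already drawn from GP records and self-report, so no new collection is needed.

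The cost is the redaction, which someone other than the rater must do, and a few sentences of definition. Using the pharmacologists would add to their workload, but no new assessor is required. All-cause readmission is less specific to drugs, which is why it accompanies the drug-related outcome and does not replace it.

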### Beliefs about Medicines will be assessed by questionnaire

- Beliefs about Medicines Questionnaire (BMQ) [26,27].

- Attitude towards prescribed medicine [28].

### Functional status of the patient

Functional status of the patient will be determined by examining the following dimensions: physical functioning, role limitation due to physical health problems, bodily pain, general health perceptions, vitality, social functioning and general mental health. These dimensions will be determined using the RAND-36 questionnaire [29].

### Patient satisfaction about prescribed medicines

Patients satisfaction will be determined using the Satisfaction with Information about Medicines questionnaire (SIMS) [30].

### Quality of life

Quality of life: mobility, self- care, main activity (work, study, housework, leisure), social relationships, pain, mood will be assessed using the EuroQol [31].

### Costs effectiveness

Costs will be registered by the pharmacists in terms of time and material spent on the counselling of patients. Health care costs made by the patient will be assessed from a societal perspective using monthly costs calendars in which direct and indirect costs will be prospectively determined by the patient. The following costs will be included in the calendars.

▪ Visits to a General Practitioner (including home visits)

▪ Visits to a medical specialist

▪ Visits to a physiotherapist

▪ Hospitalisations or admission to a nursing home

▪ Informal care (from neighbours, family or friends)

▪ Alternative medical treatment.

Costs of prescription-only medication use will be derived from the pharmacy system.

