##### Training course pharmacists

All participating intervention pharmacists will participate in a one day medication review training course. During this training session the background of medication review will be explained. The use of Medication Evaluation Profiles will be explained. Furthermore, the way the PCNE DRP-score form should be used will be explained.

To pilot test the interrater variability of the PCNE DRP-score form and the efficacy of the medication review training all participating pharmacists (controls and intervention pharmacists) will receive 5 medication overviews of test-patients with additional information about clinical notes approximately three months before the medication review training session. The results of the medication reviews will be evaluated by a specialist in medication review.

When intervention pharmacists have completed the training course in medication review, all pharmacists (control and interventions) will be asked to review five new test-patients. The intervention pharmacists are expected to detect more DRPs afterwards than control pharmacists who did not receive a special training in medication review. The results of the medication reviews will be evaluated by the same specialist as before.

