##### Training pharmacy technicians

All intervention technicians will participate in a two days training course of motivational interviewing and a one day course of problem solving treatment. During these training sessions pharmacy technicians will be lectured about communication skills such as Motivational interviewing and Problem solving treatment skills by a specialized psychologist on this subject. In addition pharmacy technicians will receive coaching on the job. Video tapes of interviews with patients will then be recorded and reviewed by two independent researchers using the Motivational Interviewing Treatment Integrity Code score method to evaluate the quality of the motivational interviewing skills of the pharmacy technicians.

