##### Pharmacotherapeutic Audit Meetings (PTAM)

In addition, to improve the intervention and its performance, the intervention will be discussed in Pharmacotherapeutic Audit Meetings (PTAM). At PTAM meetings agreements are made to improve the pharmacotherapeutic care provided. A PTAM-group generally consists of 2 to 6 pharmacists from 2 to 3 pharmacies and 6 to 10 general practitioners. During this study three PTAM sessions are organized. The first to discuss the intervention. The second to make the agreements and the third PTAM sessions are used to evaluate, the procedure.

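### The stated intervention costs cover counselling but not the pharmacist's medication review or the prescriber calls that the review requires

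*Protocol article*

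**What the plan says.** Cost-effectiveness is a stated objective (Objectives of this study) and a secondary endpoint in the abstract. Cost collection is described in one section, Costs effectiveness, which names three sources:

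- Pharmacist registration: "Costs will be registered by the pharmacists in terms of time and material spent on the counselling of patients".
- Patient calendars: "Health care costs made by the patient will be assessed from a societal perspective using monthly costs calendars". The items listed are visits to the GP, specialist and physiotherapist, admissions to hospital or nursing home, informal care and alternative treatment.
- The pharmacy system, for the cost of prescription drugs.

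Under Study procedures, the medication review is described as work done by the pharmacist. Its length is given: "The medication review will take 10-30 minutes per patient". It involves prescribers: "The GP will be consulted by telephone for details about indications for drugs and results from laboratory tests". Where a specialist prescribed the drug, the pharmacist consults the specialist about its indication, and the problems found are then discussed with the GP. Counselling is described separately as six technician sessions, at baseline and at 1, 3, 6, 9 and 12 months, of 30-60 minutes each.

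**The concern.** The intervention has two components, and the pharmacist-registered cost is worded for one of them. Calling the perspective societal makes the gap more visible, because a societal costing would be expected to count professional time whoever pays for it.

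The possible error runs in one direction. Table 1 describes usual care as computerised checks, delivery and drug information, with no structured review and no routine calls to prescribers about indications. The control arm's single technician visit only records problems for research. Time spent on reviews and calls therefore falls on the intervention arm, and omitting it lowers the estimated cost difference. The bootstrap intervals planned under Analyses describe sampling uncertainty in the costs that were recorded. They do not restore a resource that was never recorded.

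The Discussion itself describes finding and solving drug related problems as time consuming, and says the same of contacting the GP before a regimen can change.

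**Working it through.** The article gives no cost total, so there is no stated figure to reproduce. The check has two parts.

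**1. Does any listed cost source capture the review and the calls?**

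- *Counselling registration.* Setting and Study procedures assign the review to the pharmacist and the counselling to the technician. Sample size names review and counselling side by side as separate things. Talking through the review's results with the patient takes place in the sessions, so that part is covered. Carrying out the review and contacting prescribers is not covered on an ordinary reading.
- *Patient calendars.* These are filled in by the patient, and the GP and specialist items are visits. A patient would not record a call between pharmacist and prescriber.
- *Pharmacy system.* This supplies drug costs, not staff time.

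None of the three sources covers review time or call time.

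**2. How large is the review against the counselling that is registered?**

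Inputs, all from Study procedures: 6 sessions of 30-60 minutes, and a review of 10-30 minutes per patient.

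- Counselling time: 6 × 30 = 180 minutes to 6 × 60 = 360 minutes, if all six sessions are held.
- Addition from the review = review time / counselling time:
  - smallest: 10 / 360 = 2.8%
  - short review, short sessions: 10 / 180 = 5.6%
  - long review, long sessions: 30 / 360 = 8.3%
  - largest: 30 / 180 = 16.7%
- Review as a share of the combined time: 10 / (10 + 360) = 2.7% to 30 / (30 + 180) = 14.3%.

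These are shares of minutes, not of money. The review uses pharmacist time and the counselling uses technician time, and no unit cost is given for either. The article gives no duration for the GP and specialist calls, and does not say whether the pharmacist's side of them lies within the 10-30 minutes. The prescriber's own time is a further resource that cannot be sized.

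**The case against.** The strongest reply is that a short sentence in a condensed article is being read as an exclusion. The sentence does not say that nothing else is costed, and a full costing plan may exist. The word counselling is also used loosely: the section on secondary outcomes refers to a counselling visit by the pharmacist, the account of problem solving treatment puts the pharmacist in the session, and over-the-counter remedies are brought into the review during the sessions. Since the pharmacists do the registering, they may have logged their review time as well.

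This stands in part. It rules out saying that the costs were certainly omitted. It does not remove the point, because the article states a scope for intervention costs, and that scope is narrower than the intervention it describes.

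A reader might infer more than the document supports:

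- *A much larger understatement once training is added.* Training is substantial: "All participating intervention pharmacists will participate in a one day medication review training course", and "All intervention technicians will participate in a two days training course of motivational interviewing and a one day course of problem solving treatment". But minutes per patient would need an assumed number of trainees per pharmacy and an assumed length of day. Whether to charge a set-up cost to the trial's patients is also a choice of the economic evaluation.
- *A further one-sided omission for the audit meetings.* The article says: "During this study three PTAM sessions are organized". Under Treatment allocation, pharmacists are randomised within these groups, so a group can hold both arms. The meeting time is not a shown difference between arms, and session length is not given.
- *A calendar that falls short of the societal perspective,* for instance on home care or lost work. A list in an article may be abbreviated, so this is not established.
- *Roll-out decided on a flawed cost result.* The closing text links implementation to an effect on drug related problems, not to cost-effectiveness.

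**Conclusion.** The point holds in a limited and conditional form. If the cost section is followed as written, the pharmacist's review time and the GP and specialist time it requires enter no cost item, and the incremental cost of the intervention is understated. On the article's own durations the review alone adds about 3% to 17% to counselling time. This assumes that all six sessions are held and that session and review lengths stay within the stated ranges. Prescriber time is additional to the extent that it lies outside the 10-30 minutes.

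It would be wrong to conclude that the cost-effectiveness result is shown to be biased by a known amount, or that the amount is large. No unit costs or call durations are given, so no effect on the cost difference or the cost-effectiveness ratio can be computed. This is a modest correction to a secondary analysis, worth making because the error can only favour the intervention.

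**What to change.** Reword the sentence on pharmacist-registered costs so that intervention costs comprise:

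- pharmacist time for the medication review and its follow-up,
- GP and specialist consultation time arising from the review,
- counselling time and material.

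The closing text says inclusion ran from January 2008 to March 2009, so many or all reviews may already have been done and prospective logging would come too late for them. For those, estimate the time from the planned durations or from pharmacy records, and vary review time over 10-30 minutes. State whether prescriber calls are counted inside or outside that range, and label any assumed call length as an assumption. Show training as a one-off cost in a sensitivity analysis, with the number of trainees and the hours stated.

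The price is a little extra costing work and a wording change. The intervention will look somewhat more expensive. Estimates made afterwards are less exact than logged minutes, which is why the range should be reported rather than a single value.

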**Methods/Design:**

A randomized controlled trial will be performed. Community pharmacists will be randomized into a control group and an intervention group. 342 Patients, aged over 60 years, discharged from general and academic hospitals, using five or more prescription drugs for their chronic disease will be asked by their pharmacy to participate in the study.

Patients randomized to the control group will receive usual care according to the Dutch Pharmacy Standard. The medication of patients randomised to the intervention group will be reviewed by the community pharmacist with use of the national guidelines for the treatment of diseases, when patients are discharged from the hospital. The Pharmaceutical Care network Europe Registration form will be used to record drug related problems. Trained pharmacy technicians will counsel patients at home at baseline and at 1,3,6,9 and 12 months, using Cognitive Behaviour Treatment according to the Theory of Planned Behaviour. The patient's attitude towards medication and patient's adherence will be subject of the cognitive behaviour treatment. The counselling methods that will be used are *motivational interviewing *and *problem solving treatment*. Patients adherence towards drug use will be determined with use of the Medication Adherence Report Scale Questionnaire. There will be a follow-up of 12 months.

The two primary outcome measures are the difference in occurrence of DRPs between intervention and control group and adherence with drug use. Secondary endpoints are attitude towards drug use, incidence of Re-hospitalisations related to medicines, functional status of the patient, quality of life and the cost-effectiveness of this intervention.

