### Analyses

Descriptive statistics (means ± SD or median and interquartile range in case of a skewed distribution) will be used to describe the whole study sample with regard to demographics, drug use and reason for previous hospital admission. The analyses will be conducted according to the intention-to-treat principle. To assess the impact of the intervention, multilevel linear and logistic regression analyses will be conducted to study differences in outcome measures between patients of the intervention and control pharmacies. Using multilevel analyses enables taking clustering of observations of participants receiving care from the same GP and for repeated measurements within one subject in account. Differences in changes between groups are measured with 95% confidence intervals. We will adjust data for possible confounders and effect modifiers (age, sex, ethnicity, level of education). Separate analyses of effect modifiers and mediators will be conducted in order to gain a better understanding which subgroups benefit most from the intervention. Confidence intervals of differences in costs between groups will be estimated using bootstrapping methods. (Bootstrapping statistics is a general method for performing statistical analyses without making strong parametric assumptions [32].

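### Hospital costs rest on calendars kept by the patient and are not linked to the admission list the trial already compiles from GP records and self-report

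*Protocol article*

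**What the plan says.** The section Costs effectiveness adopts a societal perspective and collects health care costs "using monthly costs calendars in which direct and indirect costs will be prospectively determined by the patient". One calendar item reads "Hospitalisations or admission to a nursing home". The other items are visits to the GP, specialist and physiotherapist, informal care and alternative treatment. Two components do not depend on the calendar. Pharmacists register the time and material spent on counselling, and for drugs "Costs of prescription-only medication use will be derived from the pharmacy system".

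The section Incidence of Re-hospitalization uses a different source for admissions: "The incidence of hospital admissions will be derived from general practitioners medical record and determined by self report". Its target is narrower: "The total incidence of hospital re-admissions possibly related to medicine during the study period is measured". Criteria for a relation to drugs are then applied to the admissions found.

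The section Analyses states "The analyses will be conducted according to the intention-to-treat principle" and, for costs, "Confidence intervals of differences in costs between groups will be estimated using bootstrapping methods". On duration, the abstract says "There will be a follow-up of 12 months".

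**The concern.** A hospital stay is usually among the more expensive items in such an analysis, and a monthly diary is most likely to be neglected when a patient is unwell. The patients here are 60 or older, take at least five chronic drugs and have just left hospital. The Background itself names multiple drug use as a strong predictor of hospitalisation, nursing-home placement and death. Missing calendar months may therefore be related to the costs they should contain.

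Counselling and prescription drug costs come from the pharmacy whether or not a calendar is kept. If calendars are incomplete, the cost of delivering the intervention stays fully counted, while any saving from fewer admissions is measured with gaps.

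The gaps may also differ by arm, because the arms differ in contact with the pharmacy. At stake are the cost difference and the cost-effectiveness conclusion drawn from it.

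**Working it through.** The article gives no admission rate, unit cost or calendar return rate, so there is no figure of its own to reproduce. The check sets the sections side by side and then illustrates how the cost difference would respond to missing admissions.

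**Step 1: two sources for one event.**

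| | Re-hospitalisation outcome | Cost analysis |
|---|---|---|
| Source for hospital stays | GP record and self-report | Patient's monthly calendar |
| Scope | Admissions, then classified by relation to drugs | All hospital stays, societal perspective |
| Stated link to the other source | None | None |

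The classification works on admissions already identified. It is a reasonable inference that a list of all admissions exists before the drug-related ones are picked out. An admission on that list but on no calendar counts toward the outcome and costs nothing.

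**Step 2: contact by arm.** The section on cognitive behaviour treatment gives intervention patients sessions at baseline and at 1, 3, 6, 9 and 12 months, which makes six. The section Control Group gives control patients one visit. Both arms receive the three questionnaires. The article does not say how calendars are collected, so a difference in completeness is possible but not shown.

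**Step 3: illustration, on assumptions.** Set the true hospital cost per patient at 1.00 in the control arm. Set it at 0.64 in the intervention arm, which applies the 36% reduction in admissions cited in the Background and assumes that all admissions cost the same. The true difference is 1.00 − 0.64 = 0.36. Let m_C and m_I be the assumed shares of hospital cost missing in the control and intervention arms. Then

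observed difference = (1 − m_C) × 1.00 − (1 − m_I) × 0.64.

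| m_C | m_I | Calculation | Observed difference |
|---|---|---|---|
| 10% | 10% | 0.900 − 0.576 | 0.32 |
| 25% | 25% | 0.750 − 0.480 | 0.27 |
| 50% | 50% | 0.500 − 0.320 | 0.18 |
| 25% | 10% | 0.750 − 0.576 | 0.17 |
| 50% | 25% | 0.500 − 0.480 | 0.02 |
| 50% | 10% | 0.500 − 0.576 | −0.08 |
| 10% | 25% | 0.900 − 0.480 | 0.42 |
| 25% | 50% | 0.750 − 0.320 | 0.43 |

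Equal losses shrink the difference in proportion. Unequal losses can shrink it, reverse it or inflate it.

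**Step 4: the bootstrap.** Resampling patients reproduces the variability of the costs that were recorded. If an admission is absent from a patient's total, it is absent from every resample containing that patient. The interval is then centred on the affected difference.

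**The case against.** The strongest reply is that a prospective diary is a recognised way to collect societal costs, and that this is a condensed article. Handling of incomplete calendars, and any cross-checking of sources, may be set out in a full protocol or analysis plan that is not shown. That stands: silence on missing calendars is not an error. What remains is that the article does name a source for hospital costs, and it is not the fuller one the trial uses elsewhere.

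A second reply is that the two sections do not contradict each other. One counts re-admissions possibly related to medicines, the other costs all care. This also stands. The self-report named for admissions might even be the calendar. The point is a missed link, not an inconsistency.

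Several stronger readings are tempting but unsupported:

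- **Calendars stop at admission, decline, withdrawal or death, so the costliest months are lost.** The article does not say so. A patient may fill in the month after discharge, or a carer may help. After death no further care cost accrues, so only the months before it are at risk.
- **Costs are understated most in the arm with more admissions.** This follows if the missing share is similar in both arms. Step 3 shows that other patterns give other directions.
- **Only the large costs go missing.** GP, specialist and physiotherapy visits, informal care and alternative treatment are on the same calendars.
- **The share of patients with all 12 calendars can be found by raising an assumed monthly return rate to the twelfth power.** This assumes that months are missed independently, whereas the worry is that they cluster in ill patients. It also counts incomplete patients rather than cost lost, and says nothing about bias in the difference.

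Finally, the GP record review is described only for hospital admissions. Nothing shows that it captures length of stay, nursing-home stays or GP contacts, so it would close only part of the gap.

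**Conclusion.** The point holds as a limited one. The only stated source for hospitalisation costs is a patient-kept calendar, which is at risk of being incomplete in the sickest patients and possibly unequally by arm. A fuller list of admissions is already compiled for another outcome and is not used for costs. Neither the size nor the direction of any bias can be computed from the article. The range from −0.08 to 0.43 around a true 0.36 rests wholly on assumed costs and assumed missing shares, and shows sensitivity only. The intention-to-treat statement is harder to honour for costs if patients who stop their calendars have no other source for hospital stays. The primary outcomes are untouched; the matter concerns the secondary cost-effectiveness endpoint. It is worth correcting because the remedy draws on data the trial already plans to collect.

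**What to change.** In Costs effectiveness, state that hospital admissions will be costed from the list compiled for the re-hospitalisation outcome (GP record plus self-report). Include all admissions and not only those judged drug-related. Apply this to every included patient up to 12 months or death, including those who stop sessions or calendars, as far as consent allows. Use the calendars as a supplement and cross-check for hospital stays, and say how disagreements between the sources are settled. Keep the calendars as the source for the remaining items. Record nursing-home stays from the GP record where they are available there, with the calendar otherwise.

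The cost is modest: some further extraction, such as dates of stay, and the work of reconciling two sources. The Discussion reports inclusion as finished between January 2008 and March 2009. Extraction can still be done retrospectively, but it must be checked first that the consent already given covers this use of the records, particularly after withdrawal.
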